## Abstract

**Background:**

Up to 60% of children with Attention-Deficit/Hyperactivity Disorder (ADHD) meet diagnostic criteria for at least one anxiety disorder, including Social, Generalized and/or Separation Disorder. Anxiety in children with ADHD has been shown to be associated with poorer child and family functioning. Small pilot studies suggest that treating anxiety in children with ADHD using cognitive-behavioral therapy (CBT) has promising benefits. In a fully powered randomized controlled trial (RCT), we aim to investigate the efficacy of an existing CBT intervention adapted for children with ADHD and comorbid anxiety compared with usual care.

**Methods:**

This RCT is recruiting children aged 8–12 years (*N* = 228) from pediatrician practices in Victoria, Australia. Eligibility criteria include meeting full diagnostic criteria for ADHD and at least one anxiety disorder (Generalized, Separation or Social). Eligible children are randomized to receive a 10 session CBT intervention (Cool Kids) versus usual clinical care from their pediatrician. The intervention focuses on building child and parent skills and strategies to manage anxiety and associated impairments including cognitive restructuring and graded exposure. Minor adaptations have been made to the delivery of the intervention to meet the needs of children with ADHD including increased use of visual materials and breaks between activities. The primary outcome is change in the proportion of children meeting diagnostic criteria for an anxiety disorder at 5 months randomization. This will be assessed via diagnostic interview with the child’s parent (Anxiety Disorders Interview Schedule for Children V) conducted by a researcher blinded to intervention condition. Secondary outcomes include a range of child (e.g., anxiety symptoms, ADHD severity, behavior, quality of life, sleep, cognitive functioning, school attendance) and parent (e.g., mental health, parenting behaviors, work attendance) domains of functioning assessed at 5 and 12 months post-randomization. Outcomes will be analyzed using logistic and mixed effects regression.

**Discussion:**

The results from this study will provide evidence on whether treating comorbid anxiety in children with ADHD using a CBT approach leads to improvements in anxiety and/or broader functional outcomes.

**Trial registration:**

This trial was prospectively registered: Current Controlled Trials ISRCTN59518816 (10.1186/ISRCTN59518816). The trial was first registered 29/9/15 and last updated 15/1/19.

## Background

Attention-Deficit/Hyperactivity Disorder (ADHD) is a highly prevalent neurodevelopmental disorder affecting 5% of the childhood population [1]. ADHD causes considerable burden for children, their families and society more broadly [2]. Children with ADHD often experience comorbid anxiety disorders, which contributes to poorer functioning [3]. Effectively treating anxiety disorders in children with ADHD may improve functioning, including overall quality of life, for children with ADHD [4]. This article describes the protocol for the Calm Kids randomized controlled trial (RCT), which aims to evaluate the efficacy of treating comorbid anxiety disorders in children with ADHD using a manualized cognitive behavioral therapy (CBT) approach compared with usual care.

### Anxiety in children with ADHD

A number of studies have demonstrated that children with ADHD are at increased risk of anxiety disorders compared to their peers [3]. For example, in a large Australian study of children with ADHD (*N* = 389), 64% of children with ADHD aged 5 to 13 years met diagnostic criteria for at least one anxiety disorder, including Social (48%), Generalized (34%), and Separation (32%) Anxiety Disorders [5]. In children with ADHD, anxiety emerges early in development with 25% of 6–8 year old children with ADHD meeting criteria for an anxiety disorder (assessed via diagnostic interview) compared with 8% of children without ADHD [6].

It is clear that anxiety has an independent impact on functioning for children with ADHD. Anxiety in children with ADHD is associated with poorer attentional and executive functioning, [7, 8] social functioning, [9] and more strained family functioning (e.g., poorer parental mental health, less positive parenting behaviors) [10]. There are also established links between internalizing difficulties, including anxiety, and sleep problems in children with ADHD [11–13]. In a previous study, our group found that children with ADHD who met criteria for multiple anxiety disorders also had poorer quality of life (QoL) (effect size [ES]: − 0.8), behavior (ES: 0.4), and daily functioning (ES: 0.3) compared to children with ADHD alone [5]. Children with ADHD and multiple anxiety disorders also had higher levels of school absenteeism [5].

There appears to be a significant under-identification of anxiety in children with ADHD in clinical practice. In a large study examining pediatric consultations for ADHD (*n* = 1528), only 8% of children with ADHD were reported to have comorbid anxiety, [14] which is well below estimates of prevalence from previous studies [3]. When identified, anxiety in children with ADHD may be treated with anxiolytic medications [15]. However, psychological therapies may be preferable given the potential side effects of medications, as well as the risk of drug interactions with multiple psychotropic medications [16]. In addition, parents may be reluctant to commence pharmacological treatment for ADHD and associated comorbidities [17].

### CBT for anxiety in children with ADHD

In the general population, there is strong empirical support for a variety of skills-based strategies and packages (generally referred to as CBT) for the management of pediatric anxiety [18]. A meta-analysis found moderate effects from such interventions over waitlist conditions with anxiety remitting in 59% of children following treatment with CBT compared with 18% in waitlist controls [19]. A recent study of children aged 5 to 18 years (*N* = 842) with an anxiety disorder, examined whether comorbid ADHD (*n* = 94) influenced treatment response to CBT [20]. The study found that ADHD did not predict treatment response or rates of remission for anxiety disorders and furthermore there were small improvements in ADHD symptoms for the ADHD group following CBT [20].

Few studies have examined whether CBT is efficacious in treating anxiety in children with ADHD and comorbid anxiety, with most of them being uncontrolled and including small sample sizes. Jarrett and Ollendick [21] reported improvements in anxiety and ADHD symptom severity immediately following a 10-week CBT program for children aged 8–12 years with comorbid ADHD and anxiety (*n* = 8). Similarly, two other small studies (*n* = 7–10), found improvements in anxiety following a CBT program for children and adolescents with ADHD [22, 23]. Although Costin et al. [24] reported high levels of parent and child satisfaction following an 8-week CBT program for 7 boys with ADHD, oppositional defiant disorder and anxiety, there was no measurable improvement in anxiety, which is likely due to the high level of comorbidity in this sample.

To our knowledge only one randomized controlled trial (RCT) has examined the treatment of anxiety in children with a primary diagnosis of ADHD using CBT [4]. This small pilot study (*n* = 12, aged 8–12 years) from our research team aimed to test the acceptability and feasibility of treating anxiety in children with ADHD using CBT (a program known as “Cool Kids”) compared with usual care. The trial had good uptake (67%) and the majority of families attended all 10 intervention sessions, with no drop-outs. At 5-months post-randomization, 3/6 of intervention children were free of an anxiety diagnosis (assessed via diagnostic interview administered by researchers blinded to intervention status) compared with 0/6 of controls. Intervention children had marked improvements in child and family wellbeing by parent- and teacher-report including anxiety symptoms (effect size (ES) = − 0.6), inattention symptoms (ES = − 1.1), QoL (ES = 0.6), behavior (ES = − 0.5) and parent mental health (ES = − 1.0) [4].

### Aims and hypotheses

This RCT aims to test the efficacy of an existing CBT intervention adapted for children aged 8–12 years with ADHD and comorbid anxiety compared with usual care. Eligible children will be randomized to the intervention group (10 CBT sessions over 12 weeks) versus usual clinical care. We hypothesize that, compared with the usual care group, the intervention group will have the following outcomes at 5 and 12 months post-randomization:

### Primary outcome

Reduction in the proportion of participants meeting criteria for an anxiety disorder assessed via a researcher blinded diagnostic interview at 5 months post-randomization.

### Secondary outcomes

Fewer anxiety symptoms, measured continuously, as reported by parents, children and teacher reports at 5 and 12 months post-randomization, as well as a reduction in the number meeting criteria for an anxiety disorder at 12 months post-randomization.Reduced ADHD symptom severity at 5 and 12 months post-randomization.Improved child behavior, quality of life, sleep, cognitive functioning, and school attendance at 5 and 12 months post-randomization.Improved parent mental health, parenting behaviors, and work attendance at 5 and 12 months post-randomization.

We will also assess the cost-effectiveness of this intervention compared with usual care.

## Methods

### Overall study design

This is a RCT of CBT versus usual clinical care conducted in the state of Victoria, Australia. The trial will be reported in accordance with CONSORT guidelines for RCTs. We have prepared this study protocol adhering to the SPIRIT checklist. This trial has been prospectively registered: Current Controlled Trials ISRCTN59518816. See Fig. 1 for the participant flowchart.

**Fig. 1 Fig1:**
[figure not shown]
Participant Flow

### Participants

Participants comprise families of children aged 8–12 years with diagnostically-confirmed ADHD (see inclusion criteria) who also meet diagnostic criteria for one or more of Separation, Generalized, and Social Anxiety Disorder.

### Screening children for anxiety and recruiting families

Participants are recruited from two sources: 1. an existing database of families who had expressed interest in hearing about ADHD research; and 2. paediatric outpatient clinics in public hospitals or private pediatrician rooms in metropolitan and regional Victoria, since ADHD is commonly managed by pediatricians in Australia [14]. Across both recruitment sources families of children aged 8–12 years with ADHD (irrespective of whether anxiety has been identified given that this may be under-recognized) are mailed study letters and information booklets. An ‘opt out’ approach is used for initial contact about the study, whereby parents opt out if they *do not* wish to be telephoned by the research team to learn more about the study. If parents do not opt out within 2 weeks, the research team then telephones families to explain the study, answer any questions, and ascertain if they are interested in participating. If they are interested in hearing more, the inclusion/exclusion criteria listed below are checked.

Eligible families complete a baseline assessment visit at The Royal Children’s Hospital, their pediatrician’s office, or family home depending on preference. At this visit the parent and child each complete an electronic survey, and the child completes a direct assessment of cognitive functioning. Parents complete a study consent form and are asked to also provide consents for: data collection from their child’s teacher; data linkage access their child’s National Assessment Program-Literacy and Numeracy (NAPLAN) scores (years 3, 5, & 7); and data linkage access to their child’s Medicare/Pharmaceutical Benefits Scheme data (Australian universal subsidized health care insurance scheme) for the economic evaluation. Medicare records include services that qualify for Medicare benefits (e.g., appointments with psychologists and pediatricians) and for which claims have been processed, whereas the Pharmaceutical Benefits Scheme collects information on the prescription medications that participants have filled at pharmacies. Parents are also asked whether they consent for their de-identified data to be used for use in future studies. If parental consent is provided, the school principal is notified and teachers are invited (via email) to complete baseline and follow-up surveys assessing the child’s behavior at school.

### Inclusion/exclusion criteria (all assessed via telephone)

To be included in the trial, the child needs to meet Diagnostic and Statistical Manual of Mental Disorders (DSM) criteria 5 [25] criteria for:
ADHD: To assess this, parents are asked to rate their child’s behavior when not on stimulant medication using the 18-item ADHD Rating Scale IV - a validated scale measuring core ADHD symptoms [26]. As per DSM 5 criteria, [25] at least 6/9 inattention and/or 6/9 hyperactivity/impulsivity symptoms need to be endorsed by the parents, and the child needs to have symptom duration of at least 6 months, age of onset prior to 12 years, and evidence of impairment across settings; andGeneralized, Social and/or Separation Anxiety Disorder: This is assessed using the Anxiety Disorders Interview Schedule for Children V [27]. In our previous studies, 97% of children with ADHD and a comorbid anxiety disorder had one or more of these anxiety disorders thus we are confident that our findings will be generalizable to most children with ADHD and anxiety [5, 6].

The following exclusion criteria are also applied: non-English speaking, major child illness or disability (e.g., intellectual disability), child currently receiving CBT for anxiety, or commenced an anxiolytic/anti-depressant medication within the preceding 6 weeks. Children will be excluded if they have high levels of Autism Spectrum Disorder symptoms as indicated by scores of 15 or higher on the Social Communication Questionnaire [28].

### Sample size

A Cochrane review reported on the efficacy of CBT for children and adolescents with anxiety disorders in the general population and found remission of anxiety diagnoses in 59% of CBT participants (*n* = 808) immediately post-intervention compared with 18% in controls (*n* = 542) [19]. Taking a conservative approach, we based our sample size on observing remission in 40% of the intervention group and 20% in the control group (odds ratio of 2.7) at 5 months post-randomization (approximates post-intervention point). In order to provide 80% power to detect this clinically meaningful difference, using a two sided test with alpha = 0.05 and accounting for 20% drop-out, we need to enrol 114 children in each arm (228 total children). This sample size will enable us to detect differences of 0.42 standard deviations (SDs) between the two groups with 80% power in the continuous secondary outcomes at 5 and 12 months (using a two-sided test with alpha = 0.05). Assuming that 10% of families opt out (based on our previous ADHD trials), 47% of those contacted are eligible, and 70% of those eligible consent to participate (based on our pilot study), we need to approach approximately 771 families in order to recruit the required sample of 228 children.

### Randomization

Upon receipt of the completed consent form and completion of baseline parent and child measures, families are randomized to either the CBT or the usual care (control) group. A randomization schedule was generated using block randomization with variable block sizes by an independent statistician in the Clinical Epidemiology and Biostatistics Unit at the Murdoch Children’s Research Institute. Randomization is stratified by child sex to ensure similar proportions of males and females across groups.

Research assistants telephone families randomized to the intervention group to schedule intervention sessions at The Royal Children’s Hospital, their paediatrician’s office, or another community-based setting (e.g., school) depending on the family’s preference. Control children continue to access usual care for ADHD and anxiety from their pediatrician, which may include some simple behavioral management but is unlikely to include formal CBT [29]. All families can access other services, which may include CBT, while enrolled in the study.

Due to the nature of the intervention, it is not possible to blind participants to their allocation. Our primary outcome is a researcher-blinded diagnostic interview and we also conduct direct assessments of cognitive functioning. The comparison to usual care is essential, as we aim to evaluate whether our intervention is more beneficial than care currently received in the community. Given the importance of demonstrating longer-term benefits associated with interventions, we have opted for a usual care comparison group over a waitlist control group. Based on our previous intervention trials and pilot RCT of this intervention we do not foresee any risks or adverse effects of the intervention. Participants will be free to cease the intervention and/or withdraw from the study at any time.

### Intervention content, training & delivery

#### Content

This project uses the “Cool Kids” CBT program to treat anxiety in children with ADHD. Cool Kids has been evaluated in more than 15 clinical trials including several internationally and is currently used to treat anxiety in over 20 countries. Up to 80% of children with anxiety who have completed the Cool Kids program were diagnosis free or had substantially improved immediately post-intervention, with benefits persisting for up to 6 years [30]. Cool Kids consists of 10 sessions over 12 weeks (8 × 1 h-long weekly sessions, followed by 2 × 1 h-long fortnightly sessions), and is delivered by trained psychologists to the child and their parent(s) together. The program builds child and parent skills and strategies to manage anxiety and associated impairments. There is a strong focus on home-based skills practice. Session content is detailed in Table 1.

**Table 1 Tab1:** Session structure of the Cool Kids Program

*Session 1:* Psychoeducation, fears list/goals, worry scale, linking thoughts and feelings.	
*Session 2:* Detective/realistic thinking, rewards.	
*Session 3:* Detective/realistic thinking, design of first exposure hierarchy (stepladder).	
*Session 4:* Parenting an anxious child (parent only session).	
*Session 5*: Review of exposure progress, creative exposure, design of further stepladders.	
*Session 6*: Review of exposure progress, simplified realistic thinking, in-session exposure.	
*Session 7, 8 & 9*: Troubleshooting exposure, realistic thinking, parenting, in session exposure. Additional skills to facilitate progress: problem solving, relaxation, social skills, assertiveness, dealing with bullying, surfing emotions, testing predictions and expectations.	
*Session 10*: Review goals, maintenance of gains, setbacks, future plans.	

We have made minor adaptations to the delivery of the Cool Kids program based on our clinical expertise and experience in trials with patients with ADHD. Adaptations include: 1) use of an activity schedule and positive reinforcement to promote on-task behavior; 2) one-minute ‘brain breaks’ between activities; 3) shortening and repetition of instructions and key concepts; and 4) increased use of visual aids in sessions and at home to promote home-based skills practice.

### Follow-up

At 5 and 12 months post-randomization, the research team telephones parents to complete a researcher-blinded diagnostic interview [27] and to book a face-to-face assessment visit (same locations as described above). During these 60–90 min visits, parents and children complete surveys and a direct child assessment of cognitive functioning. The research team also e emails follow-up surveys to teachers at both time points.

### Measures

This project uses REDCap to collect survey and interview data from parents, children and teachers. Study measures are summarized in Table 2. The primary outcome is whether the child meets diagnostic criteria for one or more anxiety disorders (Separation, Social or Generalized Anxiety Disorder) measured by the Anxiety Disorders Interview Schedule for Children V at 5 months post-randomization [27]. This measure has been selected as it is rigorous, maps onto DSM criteria, and takes into account both anxiety symptom severity *and* impairment. This interview is administered by an assessor unaware of group allocation via telephone with a parent/carer parents [42]. The diagnostic interview is repeated at 12 months post-randomization.

**Table 2 Tab2:** Study measures

Construct	Measure	Source^a^	T1^b^	T2^c^	T3^d^
Primary Outcome					
Anxiety diagnoses	*Anxiety Disorders Interview Schedule for Children V:* Separation, Social, & Generalised Anxiety Disorder [27].	P	x	x	x
Secondary Outcomes					
Anxiety symptoms and impact	*Spence Children’s Anxiety Scale:* Child (44-item) and parent (38-item) reported anxiety symptoms [31].	P, C	x	x	x
	*School Anxiety Scale:* 16-items assessing anxiety symptoms at school [32].	T	x	x	x
	*Child’s Anxiety Life Interference Scale:* Child (9-items) and parent (16-items) report [33].	P, C	x	x	x
ADHD	*ADHD Rating Scale IV:* 18-item validated scale measuring the core symptoms of ADHD [26].	P, T	x	x	x
Behavior	*Strengths and Difficulties Questionnaire:* 25-items assessing child behavior and peer problems [34].	P, T, C	x	x	x
Irritability	*Affective Reactivity Index*: A 6-item validated measure assessing child irritability [35].	P	x	x	x
QoL	*Child Health Utilities Index Nine Dimension*: Preference-based measure of health-related QoL [36, 37].	P, C	x	x	x
Sleep	Single item primary caregiver report of whether the child’s sleep is a problem (none, mild, moderate or severe) [38].	P	x	x	x
School attendance	Number of days late/missed [38].	P	x	x	x
Cognitive function	*NIH Toolbox Cognition Battery:* Computer- administered assessment of cognitive and executive function, attention, episodic/working memory, and processing speed [39].	D	x	x	x
Parent mental health	*Kessler 6 (K6):* A 6-item validated measure of adult psychological stress resulting in a total score range from no distress to severe distress [40].	P	x	x	x
Parenting	*Parenting behavior:* Scales assessing parenting consistency (6-items) and warmth (6-items) [41].	P	x	x	x
Work attendance	Number of days late/missed [38].	P	x	x	x

^a^ P = parent report, T = teacher report, C = child report (completed face-to-face), D = direct assessment; ^b^ T1 = baseline; ^c^ T2 = 5 months post-randomisation; ^d^ T3 = 12 months post-randomisation

We also assess a range of other outcomes via parent, child and teacher reports (see Table 2). In addition, the baseline parent survey collects family and child demographic and medical data (i.e., medication, diagnosed comorbidities). Service use and treatments accessed are also assessed at each time point. At all time points, we conduct a direct assessment of cognitive functioning (NIH Toolbox Cognition Battery) [39] administered by a researcher.

### Data management

We use rigorous data management procedures to ensure confidentiality is maintained. The majority of the data is collected online using REDCap and can only be accessed by the research team. Hardcopy data is securely stores in locked cabinets, only accessible by the research team. All hardcopy data is entered into REDCap and subjected to data checking to ensure accuracy of data entry.

### Data analysis

Primary analyses will follow the ‘intention to treat’ principle at the child level. To account for loss to follow-up, analysis of the primary outcome (presence of Separation, Social and/or Generalised Anxiety Disorder) and all secondary outcomes will be carried out using mixed effects regression. For each outcome, a single mixed effects model will be fitted incorporating baseline, 5 month and 12 month data, adjusted for gender (randomization stratification factor), using random effects to allow for the repeated measures within an individual. These models will fit separate random effects and error terms at each time point, and a separate fixed effect of treatment at each of the two post-randomization time points. This approach implicitly deals with missing data as it enables all participants with baseline data to be included in the analysis.

For the primary outcome and other binary outcomes, groups will be compared using mixed effects logistic regression, with results presented as odds ratios and their 95% confidence intervals [CI] at 5 and 12 months. For continuous and count data secondary outcomes, groups will be compared using linear or Poisson mixed effects regression, as appropriate, with results presented as mean differences (and 95% CIs) in outcomes at 5 and 12 months. In addition, we will repeat the analysis adjusted for baseline covariates as appropriate: for example, child sex (male, female), child age, medication use (yes/no), comorbidities (yes/no), therapist, and family socioeconomic status). For our primary outcome, whether the child meets criteria for an anxiety disorder (separation, social or generalised anxiety diagnosis) at 5 months, a sensitivity analysis will be conducted using multiple imputation to handle the missing data with analysis via logistic regression applied to the 5 month data only.

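### The primary mixed logistic model takes in a baseline diagnosis that is positive for every child by inclusion, so its baseline terms cannot be estimated and the stated missing-data argument fails for this outcome

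*Protocol article*

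**What the plan says.** All places are in the Methods of the protocol article.

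- **Who enters.** Under Participants, the trial takes children with ADHD "who also meet diagnostic criteria for one or more of Separation, Generalized, and Social Anxiety Disorder". The inclusion criteria name the Anxiety Disorders Interview Schedule for Children V as the instrument.
- **What is measured.** Under Measures: "The primary outcome is whether the child meets diagnostic criteria for one or more anxiety disorders (Separation, Social or Generalized Anxiety Disorder"), on that same interview, at 5 months. Table 2 ticks the interview at baseline, 5 months and 12 months. The 12-month diagnosis is a secondary outcome.
- **How it is analysed.** Under Data analysis: "For each outcome, a single mixed effects model will be fitted incorporating baseline, 5 month and 12 month data". On structure: "These models will fit separate random effects and error terms at each time point", with a treatment effect at each of the two follow-up visits only and adjustment for the stratification factor. On the link: "For the primary outcome and other binary outcomes, groups will be compared using mixed effects logistic regression".
- **Why this is said to cope with drop-out.** "This approach implicitly deals with missing data as it enables all participants with baseline data to be included in the analysis".
- **Safeguard.** For the primary outcome, "a sensitivity analysis will be conducted using multiple imputation to handle the missing data with analysis via logistic regression applied to the 5 month data".

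The text on the single model names the primary outcome alongside the secondary ones and makes no exception for it.

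**The concern.** Putting baseline in the response vector is a sound device for an outcome that varies at baseline. It estimates a common baseline level, and the correlation between baseline and follow-up lets a child's starting value inform what is missing later. Both benefits need a baseline value that differs between children. Here it cannot differ, because the entry criterion and the outcome are the same three-disorder composite on the same interview.

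Two things are at stake. First, the primary model cannot be fitted as specified. The analyst would have to change it, and a change made after the data are seen turns the primary analysis into a post hoc choice. Second, a reader of the plan is told that baseline data protect the primary comparison against loss to follow-up, when for this outcome they do not. Missing-at-random handling then rests on arm, sex and the diagnosis at the other visit. Baseline anxiety severity, which is collected, is not part of the stated primary model.

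**Working it through.** **Planned numbers.** Inputs from Sample size: remission 40% against 20%, two-sided alpha 0.05, power 80%, drop-out 20%.

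- Two-proportion formula with continuity correction: 91 per arm.
- 91 / 0.8 = 113.75, rounded up to 114 per arm, 228 in total. This reproduces the plan's figure.
- Expected drop-outs: 0.20 × 228 = 45.6, about 46. Remaining: 228 − 46 = 182 = 2 × 91.

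**Baseline value.** Eligibility requires at least one of the three disorders on the interview, and the outcome is at least one of the same three on the same interview. The recruitment section describes surveys and a cognitive assessment at the baseline visit, with no second diagnostic interview, so the baseline value is read as the screening diagnosis. Hence y0 = 1 for every child in both arms.

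**Likelihood.** Let b be a child's random effects, in any structure, with distribution F. That child contributes

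L = ∫ P(y0 = 1 | b) · P(observed follow-up | b) dF(b).

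1. P(y0 = 1 | b) is below 1 for any finite baseline intercept and tends to 1 as the intercept goes to infinity. So L is always below ∫ P(observed follow-up | b) dF(b) and approaches it only in that limit. The baseline intercept has no finite maximum.
2. In the limit the baseline factor is 1 whatever the baseline random-effect variance or its covariances with follow-up, so these are not identified. A logistic model also has no free error term at each visit.
3. In the limit the likelihood is that of the 5- and 12-month data alone, so the treatment effects at those visits remain estimable.
4. A child with baseline only has no follow-up factor, so L tends to 1 and carries no information on treatment.

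**Numerical illustration.** One simulated trial, 2 × 114 children, y0 = 1 for all. Assumptions: shared random intercept with SD 2; about 20% missing at 5 months, most of those also missing at 12. Likelihood by 40-point Gauss-Hermite quadrature, with the baseline intercept fixed at rising values:

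| Baseline intercept | Log-likelihood | 5-month treatment log-odds of diagnosis | Random-effect SD |
|---|---|---|---|
| 2 | −231.72 | −1.470 | 0.62 |
| 4 | −205.20 | −1.694 | 1.25 |
| 6 | −197.91 | −1.941 | 1.73 |
| 8 | −195.92 | −2.111 | 2.02 |
| 10 | −195.47 | −2.184 | 2.14 |
| 20 | −195.385 | −2.205 | 2.18 |
| 30 | −195.385 | −2.205 | 2.18 |
| No baseline rows | −195.385 | −2.205 | 2.18 |

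The log-likelihood climbs throughout and flattens at the fit without baseline. Removing the 37 simulated children with baseline only changed neither the estimate nor the log-likelihood. Another 11 simulated children missed 5 months but were seen at 12; they do contribute, through the correlation between visits.

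A second simulated trial with other settings behaved the same way. With the baseline coefficient raised from 2 to 40, the log-likelihood rose from −247.85 to −214.41, the value without baseline, and the 5-month odds ratio (3.70) and random-effect SD (1.30) were the same in both fits.

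**The case against.** The strongest reply is that the diverging term is a nuisance intercept and the comparison of interest survives. That stands. In six further simulated trials (assumed random-intercept SD 1.5, 20% missing independently at each visit) with the baseline coefficient left free, the 5-month log-odds agreed with the no-baseline fit to within 0.0001 every time. The optimiser flagged non-convergence in four of the six. The distorted rows at the top of the table arise only because the intercept was held low, which maximum likelihood would not do. A reader might infer that the primary odds ratio is biased or cannot be obtained; neither follows.

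A reader might also infer that 46 children are deleted and that the trial becomes an analysis of 182. That needs every drop-out to miss both visits, which the protocol does not say. In the six runs only 7 to 14 children had neither follow-up, though that low count reflects the assumption of independent missingness. Nor is planned power lost: the sample size was inflated for 20% drop-out, and 182 is the number it was built on. Nothing shows that the results paper would misstate the number analysed; the protocol commits to CONSORT reporting.

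It is also fair that the simulations use a shared random intercept, whereas the plan has separate random effects at each visit. This limits the simulated figures to illustration. It does not rescue the plan, because the likelihood argument holds for any random-effects structure.

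Finally, imputation with logistic regression on the 5-month data avoids the problem and is already planned. It is a real but partial safeguard: it is a sensitivity analysis, and it leaves the primary model and its justification as written.

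**Conclusion.** The point holds for the anxiety-diagnosis outcome, primary at 5 months and secondary at 12. The primary model as written has a baseline term with no finite estimate and baseline random-effect parameters that are not identified. The missing-data justification is false for this outcome. The divergence follows from the constant baseline alone and does not rest on the simulation settings. It does rest on taking the baseline value to be the screening diagnosis, which is the only baseline interview the article describes.

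The size is moderate. The treatment odds ratios at both visits remain estimable, and the sample size is unaffected. The children for whom baseline inclusion is nominal number at most about 46 of 228 at the planned 20% drop-out, fewer to the extent that drop-outs are seen once. The problem does not extend to secondary outcomes that vary at baseline.

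**What to change.** For the diagnosis outcome only:

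1. Remove baseline diagnosis from the response and fit the mixed logistic model to the 5- and 12-month data.
2. Add baseline anxiety severity as covariates, from measures already collected, for example the Spence Children's Anxiety Scale and the Child's Anxiety Life Interference Scale.
3. Use the same severity measures in the multiple-imputation sensitivity analysis already planned.
4. Delete the statement that including participants with baseline data deals with missing data for this outcome, and report how many children contribute data at 5 months, at 12 months and at either.

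Making the planned imputation analysis primary would be an acceptable alternative but is not needed. A tipping-point analysis is optional.

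The cost is a change of wording, to be made before outcome data by arm are seen, and a little more analysis work. No new data are required. The one consequence to state in the plan is that the odds ratio becomes conditional on the added covariates.
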